### Follow-up assessment at 6 months

At 6 months post-discharge, all participants receive the following assessments from the RA by telephone: the sociodemographic questionnaire with embedded general health questions; the AUDIT-C; NIAAA questions regarding the number of drinks consumed per week and number of binge drinking episodes in the past 30 days; the SOCRATES; and the SIP-2R (see follow-up column, Table 2).

### Assessment of intervention fidelity (Specific aim 2)

We are assessing the five classic components of intervention fidelity: quality of delivery, exposure, adherence, participant responsiveness, and program differentiation [44]. These components are defined as follows: (1) quality of delivery: the extent to which all six FRAMES counseling components (feedback, responsibility, advice to change, menu of options, empathy, self-efficacy) [45] and three specific motivational interviewing (MI) techniques (reflective listening, decisional balance, assessment of readiness) [45] are included in the intervention; (2) exposure: the duration of the intervention (minutes); (3) adherence: the number and character of procedural deviations and interruptions to intervention delivery; (4) participant responsiveness: patient opinions about the intervention; and (5) program differentiation: the extent to which only the BI group receives alcohol-related feedback and counseling (i.e., avoiding “cross-contamination” across conditions).

Intervention fidelity is assessed for Parts I and II of the intervention using several data collection methods. First, we are audio recording 100 percent of the Part I interventions. The Study Coordinator will review 50 percent of the audio recordings (randomly selected and stratified by unit over time) to assess quality of delivery, exposure, and adherence. Barriers to intervention fidelity are assessed using several data collection methods. First, the nurse interventionist maintains narrative field notes on each intervention session, focusing on facilitators and barriers to intervention delivery and patient response to the intervention. Quality of delivery is rated using modified versions of established checklists for BI, which are based on the FRAMES model and principles of MI [45-47], upon which BI is based. For the recorded interventions and follow-up calls, we compare the interventionist’s notes to the content of the phone calls. Participant responsiveness is assessed at the conclusion of each intervention. Participants indicate their level of agreement with four statements addressing perceptions of the intervention (e.g., helpfulness, supportiveness) using a 7-point Likert-style scale, and briefly explain each answer in a free-text format below each item. Program differentiation is assessed by asking all groups at the 2-week follow-up call and the 6-month timepoint to recall the extent to which they received any additional alcohol-related feedback, recommendations, or counseling (e.g., primary care provider). These questions are embedded in the sociodemographic/clinical form.

### Nurse interventionist training

Prior to the study, the nurse interventionist, a member of the research team, received a 2-day intensive MI training led by certified trainers from the Motivational Interviewing Network of Trainers [48]. The Principal Investigator provided additional training over the course of one month that was specific to the use of BI techniques. This training included additional role-plays featuring inpatient care scenarios with staff serving as “standardized patients”, as well as training DVDs and webinars demonstrating effective BI patient interactions.

### Analysis plan

For Specific Aim 1, data analysis will focus on the change in alcohol consumption variables from baseline to 6 months across the three arms and, to the extent possible, exploratory analyses of moderators and mediators of the observed effects. The primary independent variable is the randomized treatment group. The primary outcomes of interest are: alcohol screening status, number of drinks/week (past 30 days), and number of binge drinking episodes (past 30 days). Additional outcomes include readiness to change drinking behavior and number of adverse consequences of alcohol use (for patients in Arms 1 and 2 only). Specific Aim 1 will be tested with mixed-effects regression models that account for within-patient correlation and clustering of patients within medical units. To further elucidate the impact of BI on the outcomes of interest, additional post-hoc tests for all pair-wise comparisons (i.e., BI vs. AC, BI vs. AC-LA, AC vs. AC-LA) will be conducted.

To the extent possible, we will also conduct exploratory analyses of potential moderators and mediators of effects due to the intervention. Comparisons between Arm 1 and Arm 2 can include more variables related to the underlying positive changes that BI is designed to facilitate. In particular, we will be able to explore whether the baseline SOCRATES and SIP are important moderators of change in drinking behaviors, in addition to the demographic moderators.

A sample size of 320 that complete the study (160 BI, 80 Attention Control, 80 Attention Control, Limited Assessment) will allow us to detect mean differences of 2.6 drinks per week and 0.34 points on the AUDIT-C. Sample size estimates included expected accrual of veteran inpatients into the study, duration of study participation (6 months), and number of patients expected to be lost to follow-up based on previous BI studies of hospitalized patients (20–30%) [12,14,16,40].

To characterize barriers to intervention fidelity (Specific Aim 2), we will use basic descriptive statistics (e.g., frequency counts, means, medians) to describe the numbers of deviations and interruptions to intervention delivery as planned. Based on the interventionist field notes, we will categorize the types of deviations/interruptions. We will also use these descriptive statistics to describe duration of the intervention (in minutes), the presence/absence of each FRAMES and MI technique within the intervention, and the receipt/nonreceipt of additional alcohol feedback, advice, or counseling. We will also categorize the types of additional feedback/counseling received, the provider involved, and the context in which it occurred. Participant responsiveness data (opinions about the intervention) will be analyzed with frequency counts and simple content analysis of free-text comments.

Additionally, to characterize eligibility, recruitment, and retention of participants, we will develop a recruitment funnel to assess: (a) rates of patient eligibility among hospitalized veterans; (b) rates of refusal for screening; and (c) rates of refusal for study enrollment. We will determine the: (d) mean number of telephone attempts to contact participants at 2 weeks and 6 months; and the (e) proportion of successful to unsuccessful telephone contacts at 2 weeks and 6 months. We will also categorize and generate frequency counts of reasons for: (f) patient ineligibility; (g) screening refusal, and (h) enrollment refusal.

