### Specific aims and hypotheses

The Specific Aims of this three-arm randomized controlled trial (RCT) are to: (1) determine the impact of BI on the alcohol screening status, number of drinks/week, number of binge drinking episodes, readiness to change drinking behavior, and adverse consequences of alcohol use in hospitalized hazardous drinkers; and (2) evaluate the process of intervention implementation by characterizing barriers to intervention fidelity and assessing the feasibility of recruitment, enrollment, and follow-up of hospitalized hazardous drinkers.

We hypothesize that at 6 months post-discharge, Arm 1 (BI) will report greater reductions in the alcohol consumption outcomes than Arms 2 (AC) and 3 (AC-LA). Furthermore, we hypothesize that AR will result in some reductions in alcohol consumption in Arm 2, and that the reductions in Arm 2 will be greater than those displayed in Arm 3, but less than those displayed by Arm 1.

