**Table 2 Tab2:** **Study assessments by study arm and timepoint**

		**Arm 1 brief intervention (BI)**				**Arm 2 attention control (AC)**				**Arm 3 attention control, limited assessment (AC-LA)**			
		**Timepoint**				**Timepoint**				**Timepoint**			
**Variable**	**Instrument**	**ES**	**PC**	**B**	**FU**	**ES**	**PC**	**B**	**FU**	**ES**	**PC**	**B**	**FU**
Cognitive status	Short Blessed Test	X				X				X			
Alcohol screening status	AUDIT-C	X			X	X			X	X			X
Drinks per week and Binge episodes last 30 days	3 NIAAA questions	X			X	X			X	X			X
Alcohol dependence	Modified CIDI-SAM	X				X				X			
Sociodemographic/ clinical data	Sociodemographic form		X		X		X		X		X		X
Readiness to change drinking behavior and adverse consequences of alcohol use	*Single items* from SOCRATES and SIP-2R										X		
Readiness to change drinking behavior	SOCRATES			X	X			X	X				X
Adverse consequences of alcohol use	SIP-2R			X	X			X	X				X
Participant responsiveness (patient opinions about the intervention)	4-item investigator developed instrument			X									

**Note:** AUDIT-C = Alcohol Use Disorders Identification Test, Consumption; NIAAA = National Institute on Alcohol Abuse and Alcoholism; SOCRATES = Stages of Change Readiness and Treatment Eagerness Scale; SIP-2R = Short Inventory of Problems; **Timepoints** – ES = Eligibility Screening (10–25 minutes); PC = Post Consent (5 minutes); B = Baseline (10 minutes); FU = Follow-up at 6 months (30–45 minutes).

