### Baseline assessment

The extent of patients’ baseline assessments depends on their randomization assignment (Table 2). As previously mentioned, all alcohol consumption data related to the primary outcomes are gathered by the RA during eligibility screening. All sociodemographic/clinical data are gathered immediately prior to randomization. Participants in Arms 1 and 2 are administered the Stages of Change Readiness and Treatment Eagerness Scale (SOCRATES) and the Short Inventory of Problems (SIP-2R) instruments by the RA. The SOCRATES, Version 8, is a 19-item instrument with three subscales: Recognition (of a potential alcohol problem), Ambivalence (about one’s drinking), and Taking Steps (towards behavior change) [42]. Normative data are available to aid in subscale score interpretation. We assess adverse consequences of alcohol use with the SIP-2R, a widely used 15-item, standalone, short version of the Drinker Inventory of Consequences scale [43]. This instrument assesses adverse consequences of alcohol use over the past 3 months in five areas: interpersonal, physical, social, impulsive, and intrapersonal [43]. The SOCRATES and SIP-2R instruments are not administered to Arm 3 participants to reduce the possible impact of AR. Patients randomized to the Arm 3 condition receive only two single items from the SOCRATES and SIP-2R questionnaires that are embedded within the demographic/clinical questionnaire for all participants; this allows for a coarse measure of these constructs in Arm 3 patients.

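### Readiness and adverse consequences are limited to Arms 1 and 2 although Arm 3 completes both instruments at 6 months, which rules out two of the three planned pairwise contrasts for these outcomes

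*Protocol article*

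**What the plan says.** Specific aims and hypotheses: Aim 1 covers the effect of BI on alcohol screening status, drinks per week, binge episodes, and "readiness to change drinking behavior, and adverse consequences of alcohol use in hospitalized hazardous drinkers".

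Analysis plan: "Additional outcomes include readiness to change drinking behavior and number of adverse consequences of alcohol use (for patients in Arms 1 and 2 only". The same paragraph plans mixed-effects models that allow for within-patient correlation, followed by post-hoc tests of BI vs AC, BI vs AC-LA and AC vs AC-LA on the outcomes of interest. No reason is given for leaving Arm 3 out.

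Follow-up assessment at 6 months: "At 6 months post-discharge, all participants receive the following assessments from the RA by telephone", and the list ends with "the SOCRATES; and the SIP-2R (see follow-up column, Table 2". The follow-up column of Table 2 marks both instruments for Arm 3.

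Baseline assessment: "The SOCRATES and SIP-2R instruments are not administered to Arm 3 participants to reduce the possible impact of AR". Arm 3 instead answers two single items, and "this allows for a coarse measure of these constructs in Arm 3 patients". The same sentence says that these items are "embedded within the demographic/clinical questionnaire for all participants". Table 2 has a row for single items "from SOCRATES and SIP-2R" and marks it at post-consent for Arm 3 only.

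**The concern.** The outcome data will exist in all three arms, but the analysis uses two. Arm 3 was created to show what happens without extensive assessment. By Table 2, the baseline SOCRATES and SIP-2R are what separates the assessment of Arm 2 from that of Arm 3. For the two outcomes that these instruments measure, the restriction removes the only control group that did not complete them at baseline.

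The restriction also conflicts with the plan for all pairwise comparisons, since two of the three involve Arm 3. At stake are two randomised contrasts for each outcome, from data that participants will already have given.

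**Working it through.** **1. Who has which data (Table 2, Baseline assessment, Follow-up assessment at 6 months)**

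| | Arm 1 BI | Arm 2 AC | Arm 3 AC-LA |
|---|---|---|---|
| Full SOCRATES and SIP-2R, baseline | yes | yes | no, by design |
| Full SOCRATES and SIP-2R, 6 months | yes | yes | yes |
| Single items, post-consent | unclear | unclear | yes |
| In the planned analysis | yes | yes | no |

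**2. What the missing baseline prevents.** A full-scale change score needs both time points, so it cannot be formed in Arm 3. A moderator analysis on baseline SOCRATES or SIP-2R cannot include Arm 3 either. A comparison of 6-month scores between randomised arms needs no baseline.

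**3. What is left out.** Planned completers are 160, 80 and 80 (Analysis plan).
- Share of completers: 80/320 = 25%.
- Share of controls: 80/160 = 50%.

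**4. The plan's own figures.** The detectable differences of 2.6 drinks per week and 0.34 AUDIT-C points concern other outcomes. The article gives no SD, significance level or power, so they cannot be reproduced, and nothing below depends on them.

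**5. What the omitted contrasts could detect.** Assume two-sided 5%, 80% power and unadjusted 6-month scores, in SD units:

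d = (1.960 + 0.842) × √(1/n1 + 1/n2)

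- BI vs AC, as planned: √(1/160 + 1/80) = √0.01875 = 0.1369; d = 0.384.
- BI vs AC-LA: same sizes; d = 0.384.
- AC vs AC-LA: √(1/80 + 1/80) = √0.025 = 0.1581; d = 0.443.

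**6. What pooling the controls would give.** √(1/160 + 1/160) = √0.0125 = 0.1118; d = 0.313. The ratio of standard errors is 0.1118/0.1369 = 0.816, that is, 18% smaller. The plan does not pool the controls.

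**7. Why the full-baseline model should stay.** For 160 vs 80, adjustment for the full baseline score multiplies d by √(1 − r²), and a change score multiplies it by √(2(1 − r)), where r is the assumed correlation between baseline and 6 months.

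| r | 6-month only | Change | Baseline-adjusted |
|---|---|---|---|
| 0.3 | 0.384 | 0.454 | 0.366 |
| 0.5 | 0.384 | 0.384 | 0.332 |
| 0.6 | 0.384 | 0.343 | 0.307 |
| 0.7 | 0.384 | 0.297 | 0.274 |

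Unadjusted 6-month scores are no less precise than change scores when r is 0.5 or lower. Adjustment for the full baseline is more precise at every value shown. It matches even the unadjusted pooled comparison once √(1 − r²) = 0.816, at r of about 0.58.

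**The case against.** The restriction has an evident reason, though the article does not state it. Aim 1 is analysed with repeated measures, and Arm 3 deliberately has no full baseline. This stands for change scores and baseline moderators. It does not reach a 6-month comparison.

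The impact is limited, and this stands too. These are additional outcomes. The hypotheses concern consumption, and the Discussion section on assessment reactivity judges it on drinks per week, binge episodes and screening status, all analysed in three arms. It would be wrong to infer that the trial's test of reactivity is lost.

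A reader might infer that BI vs AC-LA is the cleaner estimate of the BI effect, because the Background argues that reactivity biases results towards the null. The documents do not support this. Arm 1 also completes the full baseline instruments, so BI vs AC holds baseline assessment equal, while BI vs AC-LA estimates BI plus any effect of assessment. If the two effects add, BI vs AC isolates BI. Arm 3 also meets the instruments for the first time at 6 months, while the other arms repeat them.

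A reader might also infer an 18% gain in precision. That needs AC and AC-LA to be pooled, which the plan does not do and which presumes that reactivity is absent.

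The single items are a weak covariate: two items cannot stand in for three SOCRATES subscales and the SIP-2R. This stands, and it is a reason not to replace the full-baseline model.

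The parenthesis might be read as covering adverse consequences only. Since both full instruments are absent at baseline in Arm 3, it most naturally covers both outcomes. Even on the narrow reading, one Aim 1 outcome loses Arm 3.

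An analysis plan not shown could add detail, but the restriction is an explicit statement, and it conflicts with the pairwise plan beside it.

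**Conclusion.** The point holds for these two outcomes only. As worded, the restriction is broader than its evident reason: it excludes 25% of planned completers and removes BI vs AC-LA and AC vs AC-LA. The gain from lifting it for 6-month scores is those two contrasts, able to detect about 0.38 SD and 0.44 SD respectively. It is neither a more precise BI vs AC comparison nor a contrast free of assessment effects.

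The sizes rest on the planned 160/80/80 completers, an assumed 80% power and two-sided 5%, and no correction for multiple contrasts. That the contrasts are feasible rests only on Table 2 and the follow-up section.

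**What to change.** 1. Confine the restriction to change-score analyses and baseline SOCRATES/SIP-2R moderator analyses. Do not simply delete it.
2. Keep the Arm 1 vs Arm 2 model with full baseline scores as the main analysis of these outcomes.
3. Add three-arm 6-month comparisons of the SOCRATES subscales and the SIP-2R. Either use a longitudinal model with a common baseline mean, treating the Arm 3 baseline as missing by design, or compare 6-month scores adjusted for the randomisation strata (sex, race, unit) and, if available in all arms, the single items.
4. Report the contrasts unpooled and say what each estimates: BI vs AC, the BI effect with baseline assessment held equal; BI vs AC-LA, BI plus any assessment effect; AC vs AC-LA, reactivity.
5. Reconcile Table 2 with the Baseline assessment section on who receives the single items.

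The cost is wording and analysis time; no new data are needed. The small downside is more secondary contrasts: two added contrasts on four scores (three subscales and the SIP-2R) make 2 × 4 = 8. They should be labelled as secondary.

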**Methods/Design:**

This is a three-arm, single-site, randomized controlled trial of BI for hospitalized patients at a large academic medical center affiliated with the U.S. Department of Veterans Affairs who use alcohol at hazardous levels but do not have an alcohol use disorder. Participants are randomized to one of three study conditions. Study Arm 1 receives a three-part alcohol BI. Study Arm 2 receives attention control. To account for potential AR, Study Arm 3 receives AC with limited assessment. Primary outcomes will include the number of standard drinks/week and binge drinking episodes reported in the 30-day period prior to a final measurement visit obtained 6 months after hospital discharge. Additional outcomes will include readiness to change drinking behavior and number of adverse consequences of alcohol use. To assess differences in primary outcomes across the three arms, we will use mixed-effects regression models that account for a patient’s repeated measures over the timepoints and clustering within medical units. Intervention implementation will be assessed by: a) review of intervention audio recordings to characterize barriers to intervention fidelity; and b) feasibility of participant recruitment, enrollment, and follow-up.

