### Setting and participants

This study is being conducted on the three medical-surgical (Med-Surg) units at the University Drive campus of the VAPHS, a large academic medical center in southwestern Pennsylvania that is part of the VA. The University Drive campus is home to a 146-bed hospital facility that provides routine medical, neurological, psychiatric, and surgical care in addition to specialized services. Patient and unit characteristics for the three participating Med-Surg units are provided in Table 1.

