### Randomization

Participants are randomized to one of the three study conditions (arms) described below. Randomization assignments were generated by the study statistician prior to study start and placed in masked envelopes. Randomization sequences were stratified by sex, race, and hospital unit in a 2:1:1 ratio. This unequal allocation to the three study conditions allows more veterans to be exposed to the expected efficacious intervention and more observations to be available for analyses of mediators and moderators of positive outcomes in the BI group.

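### The analysis targets change from baseline with baseline as a repeated outcome; unless the arms share a common baseline mean, this is less precise for drinks per week than adjusting for baseline

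*Protocol article*

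**What the plan says.** The Analysis plan section states that "data analysis will focus on the change in alcohol consumption variables from baseline to 6 months across the three arms". It names the method as "mixed-effects regression models that account for within-patient correlation and clustering of patients within medical units". The abstract (Methods/Design) describes the same models as handling "repeated measures over the timepoints and clustering within medical units", so the baseline value is one of the modelled outcomes. The abstract words the target differently, however: "Primary outcomes will include the number of standard drinks/week and binge drinking episodes reported in the 30-day period prior to a final measurement visit", which is a level at 6 months and not a change.

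Three other sections bear on this. Baseline assessment says that the consumption data behind the primary outcomes are gathered at eligibility screening, which precedes randomisation in all three arms. The Discussion section on assessment reactivity says there is a single assessment after baseline. On the design, "Randomization sequences were stratified by sex, race, and hospital unit in a 2:1:1 ratio", and the setting is "three medical-surgical (Med-Surg) units".

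The article names no baseline covariate and no term for sex or race. Hospital unit is in the model, as a clustering factor. It does not say whether the arms are given a common baseline mean or separate ones.

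**The concern.** With two time points and a separate baseline mean for each arm, the arm-by-time contrast among participants with both measurements is the between-arm difference in mean change. A change score gives the baseline value a fixed coefficient of 1, whatever the data show. Baseline adjustment estimates that coefficient and so removes the variance that a wrong coefficient leaves in. The baseline value is already collected before randomisation in every arm, so the adjustment is valid and needs no new data.

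What is at stake is precision. The article's rationale is that earlier trials were driven towards the null, and its contrast between the two control arms rests on 80 completers each. Needlessly wide intervals would work against both.

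A second, smaller matter is the unit term. Three units leave 2 degrees of freedom for a between-unit variance, although patients are randomised individually within units and unit is a stratification factor.

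**Working it through.** **Inputs from the article:** 320 completers (160 BI, 80 AC, 80 AC-LA); a detectable difference of 2.6 drinks per week; three units; one follow-up; women 4% of patients on the units (Table 1).

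**Assumed, because the article does not give them:** baseline-to-follow-up correlation r = 0.3, 0.5 or 0.7; equal SDs at the two times; two-sided alpha 0.05; 80% power; contrast of 160 v 80.

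**The plan's own figure.** The 2.6 drinks per week cannot be reproduced, because alpha, power and SD are not stated. It can only be solved backwards: SD = 2.6 / [(1.960 + 0.842) × √(1/160 + 1/80)] = 2.6 / (2.802 × 0.1369) = 6.78.

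**Change against baseline adjustment.** Write s0 and s1 for the baseline and 6-month SDs.
- Var(change) = s0² + s1² − 2·r·s0·s1
- Var(baseline-adjusted) = s1²(1 − r²)
- Difference = (s0 − r·s1)², which is never negative
- With s0 = s1 = s, the ratio is s²(1 − r²) / [2s²(1 − r)] = (1 + r)/2

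| r (assumed) | Variance ratio | Simulated ratio | Completers for the precision of 320 with change, 320 × ratio |
|---|---|---|---|
| 0.3 | 0.65 | 0.67 | 208 |
| 0.5 | 0.75 | 0.74 | 240 |
| 0.7 | 0.85 | 0.86 | 272 |

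The simulation used 240 patients allocated 2:1 within three units.

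**In terms of the stated difference.** There are two readings of the SD of 6.78.
- If it is the SD of a change score, adjustment lowers the detectable difference to 2.6 × √ratio = 2.10, 2.25 or 2.40. Power at 2.6 is Φ(2.802/√ratio − 1.960) = 93.5%, 89.9% or 86.0%.
- If it is a baseline-adjusted residual SD, an unconstrained change analysis has power Φ(2.802 × √ratio − 1.960) = 62%, 68% or 73%.

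**Unit and strata.**
- Random against fixed unit effect, 60 simulated fits: mean ratio of standard errors 0.999; largest difference in the estimate 0.03 drinks per week. Many random-unit fits gave convergence or boundary warnings.
- Adding unit, sex and race to the baseline-adjusted model: variance ratio 0.995 to 1.007. For sex, a 4% stratum with an assumed effect of 0.5 SD explains 0.04 × 0.96 × 0.25 = 0.0096, about 1% of variance.
- Chance that the unit variance is estimated at or below zero, from the F distribution with 2 and 317 degrees of freedom and three equal units (320/3 each): 38%, 27% or 14% at assumed intraclass correlations of 0.01, 0.02 or 0.05.
- 95% limits for the between-unit mean square: 2/7.38 = 0.27 to 2/0.0506 = 39.5 times the estimate.

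**The case against.** The strongest objection is that the article does not commit to an unconstrained change analysis. A mixed model with within-patient correlation and a common baseline mean fits the published wording and is about as efficient as baseline adjustment. This stands, and it makes the loss conditional. It does not remove the point, because the article does state change as its target and baseline as a repeated measure, and neither statement carries that constraint.

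A related objection is that covariates are commonly left to a full analysis plan, which is not shown. That also stands: the missing mention of sex, race or a baseline covariate is not in itself an error. The point concerns the method that is stated.

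A reader might infer more than the article supports:
- **That clustering on unit or omitting strata costs precision.** Unit is already in the model, patients are randomised within units, and the checks show changes of about 1% or less. An unstable unit variance is a nuisance for fitting and hardly touches the arm contrast.
- **That baseline drinking is truncated by eligibility.** Entry is on weekly or per-occasion limits, so neither weekly drinks nor binge count is cut off on its own.
- **That the gain applies to every primary outcome.** The ratio (1+r)/2 is for a continuous measure with equal SDs. It does not carry over directly to binge counts or to screening status.

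**Conclusion.** The point holds as a free improvement in efficiency, not as an error of validity: change from baseline is unbiased under randomisation. Without a common-baseline constraint, the stated analysis of drinks per week carries variance that adjustment would remove: 35%, 25% or 15% of the change-score variance at r = 0.3, 0.5 or 0.7. These sizes rest on an assumed r, equal SDs and an approximately normal outcome. If the model already has a common baseline mean, the loss largely disappears and only the wording needs repair.

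The abstract and the Analysis plan also differ on whether the target is the 6-month level or the change, and should agree. The fixed unit effect and the sex and race terms are worth stating so that the analysis matches the stratified design and avoids a variance estimate on 2 degrees of freedom. Little or no precision should be expected from them.

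**What to change.** State in the Analysis plan that the 6-month value of each consumption outcome is compared between arms with the baseline value of the same measure as a covariate. Alternatively, specify a longitudinal model with a common baseline mean across arms, which also keeps participants without follow-up in the model. Use a model suited to counts for binge episodes and one suited to binary data for screening status. Enter hospital unit as a three-level fixed effect in place of a random cluster effect, and include sex and race as the remaining strata. Word the outcome in the abstract and the Analysis plan the same way.

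The cost is analysis wording only. Every variable is already collected, and neither the sample size nor the conduct of the trial changes.
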